### Data storage and protection

Participants’ identity or other personal information will be kept confidential. Participants will be assigned a unique ID number under which all study information will be stored in a secure file and saved on an encrypted and password-protected computer and laptop at the University of Birmingham (UoB). Physical data (e.g. case report forms (CRFs)) will be identifiable only by an ID number and stored in a locked filing cabinet at the School of Sport, Exercise and Rehabilitation Sciences at the University of Birmingham, accessible only by the research team. Participants’ personal data (name and date of birth) and consent forms matching them to their ID number will be stored securely in a locked filing cabinet, separate from all other data and/or in a password protected master sheet on an encrypted and password-protected computer and laptop at the University of Birmingham.

All serum samples will be stored in Human Tissue Act (HTA) complaint facilities at the University of Birmingham for up to 3 years then destroyed. Anonymised whole blood samples will be transferred to the University of Bologna for DNA methylation analysis on candidate genes related to nutrition and physical activity effects on the ageing process as part of an already ethically approved study which is part of the PANINI network, then destroyed at the end of the PANINI trial in Bologna (end of 2019).

All hard copy data collected on CRFs will be stored in a linked-anonymised format securely for 10 years then destroyed. All personal data (consent forms, master sheet linking participant IDs to names and contact details) will be stored for 10 years then destroyed. All computerised data will be archived on UOB servers in anonymised form for 10 years in the first instance in accordance with the UoB Code of Practice for Research, and the Data Protection Act (1998).

Following analysis for this specific study, all data will be anonymised and also entered into a European ‘PANINI’ open access database that this project is part of and optionally may be analysed in future ethically approved research across the PANINI network. The PANINI shared dataset will be made open access at the conclusion of the funding for the PANINI network including this study in 2020 and stored for at least 10 years as an open-access searchable published dataset.

## Discussion

### Implication of the research

As this is a feasibility study, the most immediate implication from a research prospective is the assessment of the feasibility of the proposed future clinical trial within this setting; which will allow for a more detailed, informative and robust understanding of the influences of the specially adapted resistance training intervention on the primary dependent variables of the future clinical trial (the multi-dimensional health and functional capacity of frail older adults within residential care settings). Additionally, frailty can also have an enormous impact on an individual’s life, in addition to the lives of their loved ones, and even an impact on society as a whole [10]. As such, if the study does prove feasible, and the limited-efficacy testing proves positive, this study also has the potential to have far reaching implications; most importantly leading to the advancement of care for frail geriatric populations within residential care settings and the ability to measurably improve various aspects of their overall health and functional ability, as well as benefitting the lives of their loved ones.

### Dissemination

The findings of this study will be disseminated through publication in the form of scientific papers in open access scientific journals, public engagement events within the UK and Europe (a core element of the PANINI project’s aims and objectives), online via social media (Twitter, Instagram) and the PANINI project website (40), presentation at various conferences within the UK, Europe and the rest of the world, and to study participants upon request, as they become available.

### Safety reporting and monitoring

Adverse events (AE) and serious adverse events (SAE) will be monitored and recorded. AE will be reviewed, while SAE will be reported immediately through completion of a SAE form indicating causality and severity (in liaison with an appropriate expert) and submitted to the study sponsor and REC within 24 h. SAE related to pre-existing conditions will not be reported. Standard actions following an AE or SAE would be a referral to a general practitioner or accident and emergency services, and to recommend that the participant withdraw from the study unless they have been cleared to continue exercise by their attending physician.

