## Background

Frailty is a common and clinically significant condition within geriatric populations [1]; the latter predominantly due to its association with adverse health outcomes such as hospitalisation, disability and mortality [1–6]. The exact prevalence of frailty within this population is poorly defined due to the lack of a single standardised operational definition for the classification of frailty. However, it is generally believed that the prevalence of frailty amongst community-dwelling older adults ranges between 7.0 and 16.3% [1, 7]. Presently, there are no well-evidenced, pooled estimates of the prevalence of frailty amongst older adults in care home settings. Although, it could be postulated that this prevalence would likely be higher than that of community-dwelling older adults, given that older adults living in care homes typically tend to be chronologically older, and often exhibit a greater number of comorbidities and a reduced functional capacity. However, these differences routinely become non-significant once standardised for age [8]. Additionally, the estimated prevalence of frailty in nursing homes (where qualified nursing care is required, in addition to care assistance) is approximately 52.3% [9]. As such, the prevalence of frailty in care homes likely lies somewhere in between that of community-dwelling older adults and nursing home residents; given the inherent nature of these respective settings, and the demographics of the individuals who occupy them.

Although there is no one standardised and universally utilised operational definition for the classification of frailty, one of the most commonly utilised is the Fried frailty phenotype [2]. This proposes that frailty be defined as a clinical syndrome in which three or more of the five following criteria are present: unintentional weight loss (≥ 10 lbs in the past year), self-reported exhaustion, weakness (grip strength), slow walking speed and low levels of physical activity.

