In order to ensure this present study is as scientifically valid as possible a number of precautions have been taken to protect the internal and external validity of the study within its methodological design. First, for each participant, all testing procedures (baseline, post-intervention (6 weeks) and follow-up (12 weeks)) will be conducted at approximately the same time of day (± 2 h). This will be controlled in order to protect the findings of the study from changes in the patient-centred outcomes which may be attributable to circadian variation rather than manipulation of the independent variable [19]. The hypothesis of the study will not be divulged to participants prior to or during the conduction of the study in order to control for any potential degree of demand characteristics; a scenario where participants alter their behaviour and/or answers, in order to align with what they believe is potentially the ‘desired’ outcome of the study. All testing sessions related to patient-centred outcomes will take place at least 24 h after the cessation of the previous training session for each participant. This will be implemented in order to ensure acute fatigue does not only become a contributing factor to the results of the study, specifically relating to the patient-centred outcomes, but also the feasibility of such practice during a proposed future clinical trial. All participants will also be asked to refrain from any relatively high-intensity exercise training up to 24 h prior to each testing session. Due to an independent measures research design being employed, a control group will be employed in order to increase the internal validity of the study, i.e. increases the likelihood that any potential changes in the patient-centred outcomes of the intervention group are due to the intervention and not additional external factors. The order in which patient-centred outcomes are tested will be counter-balanced throughout the study at each assessment time point in order to attempt to protect the study from practice effects, especially in the form of order effects, where a participant has been exposed to a specific order of testing before and as such performs better on subsequent testing procedures of the same material. Stratified-block randomisation of participants (based on frailty score and age) will also be implemented in order to reduce any differences between participants within each of the independent variable groups at baseline. This will also allow for protection against additional threats to the internal validity of the study, such as the influence of passing time (unrelated to the intervention) on participants within the study (maturation), and also protects against potential subconscious selection bias amongst the research team relating to group allocation of participants. Finally, in order to increase the external validity of the study, the eligibility criteria of this present study will be kept as minimalistic as possible (within the limits of safety and reason), in order to allow as inclusive a proportion of this population as possible, and in such producing findings which are applicable to not only those within the study, but to the greater population of frail geriatric older adults within residential care settings.

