
### Eligibility

This study is open to both men and woman whom meet the following eligibility criteria: presently, a resident within the Olivet Christadelphian Care Home, Acocks Green, Birmingham, UK; ≥ 65 years of age; frail according to the Fried frailty phenotype criteria [2]; have the capacity to speak and read in English; not currently taking part in any other clinical trial which could potentially impact upon or influence the findings of this present study; not currently terminally ill with life expectancy which is less than the duration of the follow-up of the study; does not have any severe sensory impairment which would profoundly impact upon their capacity to undergo the intervention, even once appropriate adaptations have been made.

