#### Sample size

This study aims to recruit a convenience sample of *n* = ~ 48 participants: 24 intervention and 24 regular care control. No formal power calculations were conducted due to the feasibility nature of this study. This estimated sample size is based on optimistic projections following preliminary discussion with care home residents with relation to potential uptake.

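### SAEs related to pre-existing conditions are exempt from reporting without qualification, so exercise- or testing-provoked worsening of known disease can miss the sponsor, the REC and a documented causality assessment

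*Protocol article*

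**What the plan says.** All the relevant rules stand in one paragraph of the protocol article, Safety reporting and monitoring:

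- Recording: "Adverse events (AE) and serious adverse events (SAE) will be monitored and recorded". No exception is attached.
- Reporting: "SAE will be reported immediately through completion of a SAE form indicating causality and severity", and the form is to be "submitted to the study sponsor and REC within 24 h".
- Exemption, in the next sentence: "SAE related to pre-existing conditions will not be reported".
- Standard actions (referral, and a recommendation about continuing in the study) follow any AE or SAE, again with no exception for pre-existing conditions.

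On the population, Eligibility requires residents to be "frail according to the Fried frailty phenotype criteria". Background says that older adults in care homes "often exhibit a greater number of comorbidities and a reduced functional capacity". Design overview states that "the eligibility criteria of this present study will be kept as minimalistic as possible", within limits of safety and reason. Sample size plans "24 intervention and 24 regular care control".

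**The concern.** The exemption turns on whether an event relates to a pre-existing condition. That is a different question from whether the intervention or testing caused or contributed to it. Both can be true of the same event, as when a known disease worsens after a training session. The rule lets a yes to the first question remove the event from the process in which the second is answered.

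This matters more here than in a healthy sample. Everyone enrolled has at least frailty, and Background describes frailty as clinically important because of its link with hospitalisation, disability and death, which are the kinds of event that SAE reporting exists to catch. Participants in the exercise arm undergo 21 resistance sessions in six weeks, and one-repetition-maximum testing is done on all the training machines. At stake are the sponsor's and REC's sight of possible harm during the study, and the safety evidence carried forward to a trial with a 12-week intervention.

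**Working it through.** **1. No figure to reproduce.** The article gives no expected SAE rate and no share of SAEs related to pre-existing conditions. The check is first one of reading.

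**2. Follow one event through the text.** Suppose a resident with known disease has a serious worsening after a training session.

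| Step | What the safety section says | Result for this event |
|---|---|---|
| Recording | All AEs and SAEs are recorded | Recorded |
| Standard actions | Apply after any AE or SAE | Applied |
| Causality | Indicated on the SAE form, which is the means of reporting | No stated route if the event is exempt |
| Sponsor and REC, 24 h | All SAEs, except those related to pre-existing conditions | Not sent, if the event is judged related to the known disease |

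The last two rows are the defect. The paragraph makes no exception for worsening or for possible relation to the intervention, and it does not say who judges that an event is related to a pre-existing condition.

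**3. How much could be lost (illustration only).** Let p be the probability that a participant has an SAE and q the share of SAEs exempted. Neither is in the article; both are assumed. With 24 in the exercise arm, at most one SAE per participant and independence:

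- expected reported = 24 × p × (1 − q)
- chance of at least one report = 1 − [1 − p(1 − q)]^24

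For p = 10% and q = 0: 24 × 0.10 = 2.4 expected, and 1 − 0.90^24 = 0.920. For p = 10% and q = 50%: 24 × 0.05 = 1.2 expected, and 1 − 0.95^24 = 0.708.

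Chance of at least one reported SAE (expected number reported in brackets):

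| Assumed p | q = 0 | q = 25% | q = 50% | q = 75% | q = 90% |
|---|---|---|---|---|---|
| 5% | 0.708 (1.2) | 0.600 (0.9) | 0.455 (0.6) | 0.261 (0.3) | 0.113 (0.12) |
| 10% | 0.920 (2.4) | 0.846 (1.8) | 0.708 (1.2) | 0.455 (0.6) | 0.214 (0.24) |
| 20% | 0.995 (4.8) | 0.980 (3.6) | 0.920 (2.4) | 0.708 (1.2) | 0.384 (0.48) |

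The effect runs from slight to large depending on q. The table shows how the exemption would act; it does not estimate the loss in this trial.

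**The case against.** The strongest reply is that the disputed sentence directly follows the 24 h submission rule and is best read as limiting that expedited route only. Recording is stated without exception, non-serious AEs are untouched, and the standard actions apply to every AE and SAE, so neither the study record nor the immediate handling of a resident depends on the form. That stands, and it narrows the point to notification and documented causality.

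It can also be said that a condensed article leaves definitions to the full protocol. That is fair for who decides and for what counts as pre-existing, and the full protocol may qualify the rule. But the exemption itself is stated, and stated without limits. It is not a missing detail.

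Three stronger readings are tempting and are not supported:

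- *Most of the safety signal is removed.* This needs q above 50%, and the article describes comorbidity only in words.
- *Zero reported SAEs would hide a very high true risk.* For 0 of 24, the one-sided 95% upper bound is 1 − 0.05^(1/24) = 11.7%. Dividing by the reported share gives 11.7/0.75 = 15.6% at q = 25%, and 23.5%, 39.1% and 58.7% at q = 50%, 70% and 80%. The answer is set by the assumed q. It also treats expedited reports as the only SAE data, which the recording sentence contradicts.
- *The between-arm safety comparison becomes uninterpretable.* The article describes no such comparison, and nothing says that a tabulation would be confined to the reported forms.

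**Conclusion.** The point holds as a defect in the reporting rule. As written, an SAE that is a worsening of known disease, including one provoked by exercise or strength testing, can go unreported to the sponsor and REC and have no documented causality assessment. This follows from the text alone, given that causality is indicated on the form used for reporting and that every participant is frail.

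The size of the loss is unknown. Under assumed values of p = 10% and q between 25% and 75%, the chance of at least one report from the exercise arm falls from 0.920 to between 0.846 and 0.455, but the documents support no particular value. The conclusion assumes that the rule is applied literally and that the full protocol does not limit it. It should be corrected because it concerns participant safety and the change is small.

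**What to change.** Remove the exemption as a filter that acts before causality is assessed. Specifically:

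1. Complete the SAE form for every SAE in both arms, including causality to the intervention or to testing.
2. Add a yes/no field for relation to a pre-existing condition, used as a descriptor beside causality and not as grounds for leaving the form undone.
3. State that no SAE that is a worsening of a pre-existing condition, or is possibly related to the intervention or testing, is withheld from the sponsor and REC.
4. Tabulate all recorded SAEs by arm, showing relation to pre-existing conditions and causality.

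The cost is an amendment to one sentence, one field on the form, and a few more SAE forms in a study of about 48 people. Recording and clinical handling stay as they are.

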### Trial registration

This study has been registered on ClinicalTrials.gov under the identifier number NCT03141879.

### Trial status

This trial has received ethical approval and is due to be conducted in 2019 at the Olivet Care Home, [name], with completion of data collection scheduled prior to 01 December 2019.

## Data Availability

Not applicable.

## Abbreviations

1RM: One repetition maximum
ADL: Activities of daily living
AE: Adverse events
ANOVA: Analysis of variance
CRF: Case report form
CRP: C-reactive proteins
DHEAS: Dehydroepiandrosterone
ELISA: Enzyme-linked immunosorbent assay
GDS: Geriatric Depression Scale
HADS: Hospital Anxiety and Depression Scale
HTA: Human Tissue Act
IFNy: Interferon gamma
IL-6: Interleukin-6
IPA: Interpretive Phenomenological Analysis;
ISEL-12: Interpersonal Support Evaluation List-12
KARE: Keeping Active in Residential Elderly
NHS: National Health Service
PANINI: Physical Activity and Nutritional INfluences In ageing
PI: Principal investigator
PPI: Patient and Public Involvement
PSS: Perceived Stress Scale
REC: Research Ethics Committee
SAE: Serious adverse events
SMMSE: Standardised Mini-Mental State Examination
SPPB: Short physical performance battery
SPSS: Statistical Package for Social Sciences
TNFα: Tumour necrosis factor alpha
